### Covariates

Annual information on parental leave uptake (number of days) for each parent will also be available from LISA. Specific information on parental leave eligibility and uptake (including length of paid and unpaid leave) will be retrieved from the SIAD.

Demographic characteristics will include parents’ age at childbirth, country of birth (ie, Swedish vs other and specific origins) and marital and cohabitation status, from the TPR and LISA. Sociodemographic characteristics including educational attainment, household disposable income, individual labour income, employment status and receipt of sick leave benefits will be drawn from LISA.

### Study design and statistical analyses

A variety of advanced designs and statistical methods for observational data will be applied. First, using descriptive and correlational designs, we will implement standard multivariable methods to quantify links between prebirth health conditions, parental leave eligibility and uptake, and postbirth health outcomes while accounting for confounding using relevant covariates and heterogeneity analyses.

Second, we will use robust quasi-experimental approaches to assess the causal effects of parental leave policy on health, reducing the risk of selection effects and unmeasured confounding by harnessing the natural, ‘as-if’ randomisation around policies.^45 46^ With this approach, we can isolate the absolute policy effects on health even in the absence of detailed information on changes in parental leave uptake. These approaches include interrupted time series (ITS), regression discontinuity (RD) and difference-in-difference (DiD) designs. For ITS designs, segmented regression models will be adjusted for seasonality and trend while accounting for autocorrelation.^46^ For RD designs, continuity around the cut-off will be tested using the McCrary Density Test and similarity of eligible and ineligible observations will be determined through descriptive statistics. Finally, for DiD designs, we will examine the data to confirm parallel trends and other relevant assumptions.^45^

RQ#1: We will examine the effects of the 2002 doubling of flat-rate benefits on the mental health of parents. An RD design will be applied to plot psychiatric hospitalisation rates with labour income as a forcing variable, with separate plots before (with an income cut-off equivalent to 75 SEK, at 80% reimbursement rate) and after 2002 (with a cut-off equivalent to 150 SEK daily). Cut-offs for both parents’ income will be examined. We will triangulate our findings with a DiD approach, comparing those eligible for the increased benefits to those ineligible before and after reforms.

RQ#2: A segmented-regression ITS of monthly birth data comparing the rate of low birth weight and preterm births 3 years before and after the 1980 and 1986 speed premium reforms will be implemented. We will also compare the prevalence of obesity in mothers early in their second pregnancy before and after the reform.

RQ#3: We will conduct an ITS analysis of parents of children born before and after the 1995 father’s quota reform using segmented regression to capture changes in psychiatric hospitalisation rates up to 36 months after childbirth, based on fathers’ eligibility for the father’s quota.

RQ#4: An ITS for parents to children born before and after the 2012 double days reform will be implemented to capture changes in the number of outpatient visits for mental health and psychotropic prescriptions within 36 months after childbirth, by child’s month of birth.

RQ#5: We will implement separate ITS analyses of children born before and after the 1995 father’s quota and 2012 double days reforms, comparing hospitalisation rates for diagnoses of respiratory tract infections (in children under 2), prevalence of childhood obesity (at 18 months and 3–5 years) and changes in breastfeeding duration.

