### Additional analyses

Given the potential for effect modification and compositional changes in the study populations, subgroup analyses by parents’ sociodemographic characteristics (ie, annual labour income, to determine eligibility for earnings based benefits or educational attainment) will be considered for all RQ. Analyses by parents’ nativity will be implemented for RQ#2–4, given differential responses to the policies by Swedish-born and foreign-born parents.^14^ Other relevant parental characteristics, that is, age at childbirth and cohabitation status, will also be considered.

Sensitivity analyses will be performed to account for systematically missing data, such as maternal weight (ie, given that women appearing to be of normal weight are less monitored for obesity).^47^ For studies examining first births, sensitivity analyses restricting mental health outcomes to the 18 months post birth will be considered in order to exclude the potential health effects related to a second pregnancy.

For all ITS designs, we will specify multiple intervention points to assess the possibility of lagged policy effects. Robustness analyses of falsification (‘pseudo-intervention’) dates and falsification outcomes (eg, prebirth hospitalisations) will also be considered.

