### Limitations

Despite our reliance on a robust quasi-experimental approach, it is difficult to predict the relative timing of the behavioural response to each parental leave reform (ie, in uptake) and its health consequences. Parents have been shown to respond quickly to policy changes,^14 15 27^ but given that some parents may not be aware of their eligibility on the reform dates, delayed reaction times could lead to lagged health effects for subgroups such as migrants.^12^ Thus, we will use a long follow-up both within the life course (ie, years since birth) and in the context of the policy (ie, years since reform implemented).

Quasi-experimental designs have the potential to reduce unmeasured confounding, but policies themselves, as well as ongoing trends, could inadvertently modify the composition of the study populations, potentially biasing any causal interpretations. For one, the speed premium may have affected the composition of individuals who decided to have children after the reform, that is, encouraging more parents eligible for earnings based benefits to have children after 1986, given their increased level of benefits for subsequent children. Exogenous impacts other than the policy under investigation could also contribute to changing population compositions, as in the case of the 1990s economic crisis, which may have discouraged couples with lower socioeconomic position from having children after the 1995 father’s quota. We will thus examine varying sociodemographic characteristics of the study populations before and after each reform to assess the robustness of the design to approximate causal effects, with corresponding subgroup and sensitivity analyses.

Registers generally have greater coverage than other data sources but may be prone to bias in the form of missing data and overcoverage (ie, unreported outmigration), which we will address in appropriate sensitivity analyses. The historical availability of register data may also influence our analytical choices. For example, to evaluate the impact of the father’s quota on psychiatric health, we will primarily look at the first reserved month introduced in 1995.^6^ However, only severe health outcomes (psychiatric hospitalisations) can be assessed with the available registers at that time. In order to evaluate less severe outcomes (outpatient visit and prescription data) of increased fathers’ leave use, we will evaluate the more recent double days reform.^16^

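### The causal models for RQ#1, RQ#3 and RQ#4 name no pre-birth psychiatric care, so an abrupt or differential shift in parents' psychiatric history could be read as a reform effect

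*Protocol article*

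**What the plan says.** All places are in the protocol article.

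- **ITS (RQ#3, RQ#4).** Under Study design and statistical analyses, "segmented regression models will be adjusted for seasonality and trend while accounting for autocorrelation". RQ#3 applies this design "using segmented regression to capture changes in psychiatric hospitalisation rates up to 36 months after childbirth". RQ#4 applies it to "capture changes in the number of outpatient visits for mental health and psychotropic prescriptions within 36 months after childbirth".
- **RQ#1.** "An RD design will be applied to plot psychiatric hospitalisation rates with labour income as a forcing variable". The accompanying DiD is described as "comparing those eligible for the increased benefits to those ineligible before and after reforms". Neither description names a measure of baseline health.
- **Covariates.** The list holds leave uptake, demographic items and socioeconomic items. Receipt of sick leave benefits is the only health-related entry.
- **Pre-birth health.** It has two uses. The descriptive and correlational analyses will "quantify links between prebirth health conditions, parental leave eligibility and uptake, and postbirth health outcomes while accounting for confounding using relevant covariates". For the ITS designs, Additional analyses adds that "falsification outcomes (eg, prebirth hospitalisations) will also be considered".
- **Data.** Inpatient care is available from 1964, outpatient care from 2001 and prescriptions from 2005.
- **Composition.** Limitations accepts that a changing study population could bias causal readings. It gives the 1990s economic crisis as an example, "which may have discouraged couples with lower socioeconomic position from having children" after the 1995 reform. The response is to compare sociodemographic characteristics before and after each reform, with subgroup and sensitivity analyses.

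**The concern.** The Abstract says the quasi-experimental designs are meant to reduce the risk of health selection. The section on unintended health consequences explains one route: long-term illness weakens labour market attachment and so eligibility for earnings-based benefits. The most direct register measure of that selection, for a psychiatric outcome, is the same parent's earlier psychiatric care. It is already linked, and for a first birth a pre-conception value precedes any leave taken for that child. Yet it has no firm role in the causal analyses.

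A falsification test on pre-birth admissions can show that the health mix moved, but it does not take the movement out of the estimate. Income, education, nativity and sick leave benefits are related to psychiatric history but need not follow it closely. The risk is that a change in who becomes a parent around 1995, 2002 or 2012 is credited to the reform. RQ#1 deserves particular care: its groups are defined through income, which the article itself links to health.

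**Working it through.** The article states no sample size, power, event rate or correlation, so there is no figure to reproduce. Every input below is an assumption, shown as a range.

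**1. Size of a composition artefact.** Let p0 and p1 be the shares of parents with psychiatric history before and after the reform, and RR the ratio of their post-birth rate to that of other parents. With no reform effect,

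spurious rate ratio = [1 + p1(RR − 1)] / [1 + p0(RR − 1)].

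For a 10% relative rise in the share:

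- p0 = 2%, p1 = 2.2%, RR = 5: 1.088 / 1.080 = 1.007
- p0 = 5%, p1 = 5.5%, RR = 10: 1.495 / 1.450 = 1.031
- p0 = 10%, p1 = 11%, RR = 20: 3.09 / 2.90 = 1.066

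The range is about 1.01 to 1.07. Rises of 20% to 25% give 1.019 (2% to 2.5%, RR 5) to 1.131 (10% to 12%, RR 20).

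**2. What the segmented model does with it.** The middle case (p0 = 5%, RR = 10, 10% relative change) was passed through a 72-month segmented regression on the log rate, with terms for level, trend, change in level and change in slope:

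| Shape of the shift | Spurious level change | Spurious slope change per year |
|---|---|---|
| Smooth drift over 6 years | 1.000 | 1.000 |
| Step at the reform | 1.031 | 1.000 |
| Ramp over the 12 months before | 1.015 | 0.993 |
| Ramp over the 3 years after | 1.000 | 1.010 |

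Only a shift that departs from the modelled trend near the reform matters.

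**3. DiD and RD.** DiD removes stable differences between groups. If the share steps in one group and not in the other, the formula in step 1 applies to the contrast itself, with the same 1.01 to 1.07 for a 10% step. A valid RD needs no baseline covariate to be unbiased; there, pre-birth care serves to check validity.

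**4. Precision.** The standard error (SE) after adjustment is multiplied by √(1 − R²).

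- *Hospitalisation (RQ#1, RQ#3).* For outcome risk q, share p and risk difference d by history, R² = p(1 − p)d² / [q(1 − q)]. With q 0.5% to 2%, p 2% to 10% and RR 5 to 20, R² runs from 0.001 to 0.092. The SE falls by 0.1% to 5%.
- *Visit and prescription counts (RQ#4).* With pre/post correlation r, R² = r². For r = 0.3, 0.5 and 0.7 the factor is 0.954, 0.866 and 0.714, so the SE falls by about 5%, 13% and 29%.

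**5. Look-back available.** Inpatient data from 1964 cover RQ#1 and RQ#3. For RQ#4, prescriptions start in 2005, so a look-back reaching 36 months before birth is complete for births from about 2008. That leaves about four of the seven pre-reform years (2005 to 2011). Outpatient data from 2001 allow the same look-back for births from 2004.

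**The case against.** The strongest reply is that this is a condensed article. A full covariate set may sit in a document not shown, and silence is not exclusion. That is fair as far as it goes: nothing in the text rules the adjustment out. But the article does state its ITS adjustment terms, its covariates and its response to composition change, and pre-birth psychiatric care is in none of the three.

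A second reply is that safeguards exist: pseudo-intervention dates, pre-birth falsification outcomes, subgroup analyses, the McCrary test, RD similarity checks, parallel-trends checks and before/after comparisons that could include sick leave benefits. These stand and lower the risk. However, the falsification analyses are only to be considered, the RD similarity variables are not named, and none of the safeguards removes a shift in psychiatric mix.

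A reader might also infer more than the documents support:

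- *That pre-birth health is used nowhere else.* The correlational analyses commit to it.
- *That the estimates are biased.* No part of the article documents an abrupt shift in psychiatric history at any reform date. The 1990s crisis is offered as an outside influence on composition, not as a step in January 1995.
- *That raw before/after arithmetic gives the bias.* A fall in the share from 3.0% to 2.5% with RR 8, 15 or 25 lowers the crude rate by 2.9%, 4.9% or 7.0%. That contrast has no trend term and is not the planned model.
- *That power rises from 80% to 90%.* This needs a correlation of 0.5 and an assumed 80% start. For hospitalisation at an assumed 1% risk and p = 3%, those same RR values imply correlations of only about 0.10, 0.17 and 0.24.

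**Conclusion.** The point holds in a limited form. The causal analyses for RQ#1, RQ#3 and RQ#4 name no adjustment for parents' pre-birth psychiatric care, although the article identifies health selection as a threat and has the data to address it. The exposure is conditional: an abrupt shift at the reform date for the ITS, or a differential shift between eligible and ineligible parents for the RQ#1 DiD. Smooth drift does no harm, and a valid RD is unaffected.

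If a 10% relative step occurred, the spurious rate ratio would be roughly 1.01 to 1.07, assuming 2% to 10% of parents have a history and a rate ratio of 5 to 20. Whether such a step occurred cannot be judged from the document. The precision argument is negligible to small for hospitalisation. It is worth making only for the RQ#4 counts, where the SE would be about 5% to 29% lower if the pre/post correlation is 0.3 to 0.7.

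**What to change.** 1. For the RQ#1 DiD, RQ#3 and RQ#4, report beside the planned model a second one that adjusts for, or stratifies by, each parent's psychiatric care in a fixed pre-conception look-back. Use admissions for RQ#1 and RQ#3, and outpatient visits and prescriptions for RQ#4. The window should have the same length for every birth.
2. Add the same variable to the before/after composition comparison and to the RD similarity check.
3. Make the pre-birth falsification analysis definite, and report it separately from the adjusted model.

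The cost is analysis wording and modelling on registers already in the plan, with three limits to state. First, a 36-month look-back restricts the adjusted RQ#4 prescription series to births from about 2008. A shorter window keeps more pre-reform months, and showing the planned model alongside keeps the full series in view. Second, recent immigrants lack Swedish register history for part of the window and need a missing-history indicator. Third, in the secondary multiparous analyses the look-back can overlap leave for an earlier child, so the adjustment should be confined to first births.

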#### Parental leave eligibility and compensation

In Sweden, all legally residing parents are eligible to receive parental leave benefits (ie, job-protected leave), including biological parents as well as individuals with child custody.^10^ Individuals must apply for these benefits through the Social Insurance Agency, the governmental authority that decides on and administers insurance and contributions to families and children in Sweden.^11^ The benefits are split into general flat-rate or earnings based benefits, collectively referred to as ‘parental benefits’ and applied to 390 out of the total 480 days, while the remaining 90 days are paid at a second flat rate, henceforth referred to as ‘guarantee days’.^7^

To be eligible for earnings based parental benefits, an individual must have been employed for at least 240 consecutive days prior to the estimated delivery date with a minimum annual income of 82 100 Swedish kronor (SEK) (in 2020). Although the remuneration level has varied over time, individuals today receive approximately 80% of their salary up to a certain ceiling (1006 SEK per day in 2020) from the Social Insurance Agency, with potential top-ups from the employer.^12^ If an individual has an income below a certain level (117 590 SEK in 2020) during the 240 days before childbirth, they are only entitled to a general flat-rate benefit (250 SEK per day in 2020) for the first 180 days which they claim for the child. After 180 claimed days, parents can receive benefits based on their current earnings.^7^ Finally, if an individual has no income or an annual income below the stipulated level throughout the leave period, they will receive the general flat-rate benefit for the full 390 days. However, if an individual is sick, a student or unemployed but a ‘job seeker’, they can receive parental leave benefits based on their prior income if they have registered with the Public Employment Service.^10^ Regardless of employment history, the final 90 days are always paid at a minimum guaranteed level of 60 SEK starting in 1987 and 180 SEK since 2006.^7^

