#### Policy reforms

The Swedish parental leave system has undergone several reforms over the past half-century. We define a ‘policy reform’ as any change implemented at a specific time that could impact either uptake or sharing of parental leave, as well as eligibility for earnings based benefits. To evaluate the unforeseen health consequences of the parental leave policy—that is, a welfare policy that does not primarily target health—we will concentrate on reforms that have either been shown to accomplish their primary aim (ie, the speed premium, father’s quota and double days reforms) or with undoubtedly significant, although unintended, impacts (ie, the doubled value of general flat-rate benefits).

Doubled flat-rate benefits: Although not explicitly a reform, the doubling of the general flat-rate benefits from 60 SEK per day (from 1987) to 120 SEK per day (in 2002) aimed to secure the economic welfare of low-income families.

Speed premium: Since earnings related parental leave benefits are estimated based on one’s salary prior to childbearing (at approximately 80% of the salary), parents having children in quick succession may choose to temporarily reduce their working hours or be unable to return to work at all and will thus have lower benefits for their second and subsequent births. In 1980, a supplement (commonly referred to as the ‘speed premium’) was introduced to safeguard women’s income between parental leave periods, ensuring that for births with up to 24 months’ spacing^13^ and then with up to 30 months’ spacing (following a 1986 expansion),^14^ all earnings based benefits could be based on the parents’ salaries prior to the birth of their previous child, if higher than their current income. An evaluation of the 1986 expansion revealed that an increased proportion of Swedish-born parents had children in short succession; even if this was an unintended consequence, the reform has henceforth been called the ‘speed premium’.^14^

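### The RQ#1 regression discontinuity is placed at incomes where the benefit changes slope but does not jump, so a null result there would be uninformative

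*Protocol article*

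**What the plan says.** The Policy reforms section describes "the doubling of the general flat-rate benefits from 60 SEK per day (from 1987) to 120 SEK per day (in 2002". The section on eligibility and compensation says that "individuals today receive approximately 80% of their salary up to a certain ceiling", and that parents with income below a threshold are in a different position: "they are only entitled to a general flat-rate benefit (250 SEK per day in 2020) for the first 180 days". After those days, benefits can follow current earnings.

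The RQ#1 paragraph of Study design and statistical analyses builds the RD on these rules: "An RD design will be applied to plot psychiatric hospitalisation rates with labour income as a forcing variable". There are separate plots for the two periods, the first "with an income cut-off equivalent to 75 SEK, at 80% reimbursement rate" and the second "with a cut-off equivalent to 150 SEK daily". The checks named for RD designs are a McCrary density test and a descriptive comparison of observations on the two sides. A DiD across the reform is planned to triangulate the result, contrasting parents who stood to gain from the increase with those who did not. No slope or kink estimand is mentioned.

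**The concern.** An RD identifies an effect from a jump in treatment at the cut-off. The two cut-offs appear to have been derived by asking at what income the earnings-based benefit catches up with the flat rate. At that income the two formulas pay the same, so the parent just above and the parent just below receive the same amount.

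RQ#1 asks whether eligibility for earnings-based benefits is associated with parents' mental health. If the RD shows no jump, the natural reading is that eligibility does not matter. Because the DiD is there to triangulate, a flat RD could also be held against a DiD that had found a real effect. The planned RD checks look for sorting and imbalance around the cut-off; they do not ask whether the treatment changes there.

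**Working it through.** **Inputs.** Flat rate F: 60 SEK per day from 1987, 120 SEK in 2002 (Policy reforms). Replacement rate: about 80% (eligibility section and RQ#1 paragraph). Cut-offs: daily income 75 and 150 SEK (RQ#1 paragraph).

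**1. Reproducing the cut-offs.** Cut-off = F / 0.80. 60 / 0.80 = 75 and 120 / 0.80 = 150, both exact.

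**2. Benefit around the cut-offs.** With B(w) = max(F, 0.80w):

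| Period | Income just below | At cut-off | Just above |
|---|---|---|---|
| Before 2002 | 74: 60 SEK | 75: 60 SEK | 76: 60.8 SEK |
| After 2002 | 149: 120 SEK | 150: 120 SEK | 151: 120.8 SEK |

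The jump is 0.80 x 75 - 60 = 0 and 0.80 x 150 - 120 = 0. The slope goes from 0 to 0.80.

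**3. What a local-linear RD would find.** Let the outcome be a smooth function of income plus b x (B(w) - F), where b is the effect per SEK of daily benefit. The limits from the left and right at the cut-off are equal, so the expected jump is 0 for every b. The slope changes by 0.80b. A simulation at the 150 SEK cut-off illustrates this. Its settings are assumptions, not taken from the article: base rate 1%, a smooth income gradient, incomes uniform within 50 SEK either side, 200 000 observations, 60 runs.

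| b per SEK | Effect of +60 SEK (percentage points) | Mean RD jump (SD per run), points | Mean slope change / 0.80 (SD per run) |
|---|---|---|---|
| 0 | 0 | -0.020 (0.087) | 0.0000046 (0.0000338) |
| -0.00002 | -0.12 | -0.006 (0.089) | -0.0000148 (0.0000345) |
| -0.00005 | -0.30 | -0.014 (0.107) | -0.0000573 (0.0000344) |
| -0.0001 | -0.60 | -0.015 (0.103) | -0.0000962 (0.0000328) |

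The RD jump is noise around zero in every row, while the slope change follows b. A crude difference in mean rates between the two sides is not zero, but it is about -0.05 points even when b = 0, because it absorbs the income gradient. It is not an RD estimate.

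**4. Sensitivity to the rate.** The article says approximately 80%. Its 2020 figures give 0.80 x 117 590 / 365 = 258 SEK against a flat rate of 250, an implied rate of 250 x 365 / 117 590 = 77.6%. If the rate were 75% to 85% and the benefit switched formula exactly at the cut-off, the jump would be 0.75 x 75 - 60 = -3.75 to 0.85 x 75 - 60 = +3.75 SEK before 2002. After 2002 it would be -7.5 to +7.5 SEK. Against the 60 SEK rise of the reform that is at most 3.75 / 60 = 6.25% and 7.5 / 60 = 12.5%. If the higher amount is always paid, the jump is 0 at any rate, and the kink moves to F / rate.

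**5. Other reading of the cut-offs.** Taken as benefit amounts, 75 and 150 SEK correspond to incomes of 75 / 0.80 = 93.75 and 150 / 0.80 = 187.5. The schedule has neither a jump nor a kink there.

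**6. Later years.** The flat rate was 250 SEK in 2020. At that rate parents on both sides of 150 SEK receive the flat rate (0.80 x 150 = 120, below 250), so a fixed cut-off would eventually lose the kink too.

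**7. Where the reform does create contrast.** Gain = max(120, 0.80w) - max(60, 0.80w): 60 SEK at incomes up to 75, 40 at 100, 20 at 125, 0 from 150.

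**The case against.** The strongest reply is that RQ#1 does not rest on the RD alone. The article names no primary analysis for it, and the DiD exploits the change at fixed income, which does not depend on a jump. That stands. A reader might infer that RQ#1 has no treatment contrast at all; the article does not support that.

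Second, the article speaks of plotting rates and gives no local model or bandwidth, which may be in an analysis plan not shown. That is fair, and a slope change in the same plots could be informative. But the article itself fixes the design type, the forcing variable and the cut-offs, and without a slope estimand the ordinary meaning is a jump.

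Third, eligibility might bring something besides the daily amount; the eligibility section mentions employer top-ups. It does not say they begin at this income, so this does not restore a jump. It does rule out the claim that the RD must return zero whatever the true effect: the argument covers a level jump driven by benefit amount.

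Fourth, the schedule is not a simple maximum, because of the rule for the first 180 claimed days. If current earnings equal earnings before birth, a parent just under the cut-off moves after those days to just under 60 or 120 SEK, so there is still no material jump. That equality is an assumption. The article does not say what floor applies after those days at lower incomes, so the argument should not be extended to its other income threshold.

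Two more inferences should be resisted. One is that the density test would pass: a kink can itself induce bunching, so the supportable statement is only that the test is not designed to reveal a missing jump. The other is that the forcing variable is wrong because entitlement depends on the 240 days before delivery. The article does not say which year's labour income is meant, and it plans to take eligibility information from the Social Insurance Agency database.

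**Conclusion.** The point holds as a defect in where the RD is placed. On the article's own figures the daily benefit does not jump at 75 or 150 SEK; it changes slope from 0 to about 0.8. A level-jump RD on benefit amount has essentially no contrast there, and a null would say nothing for or against an effect of benefits on mental health, or about the credibility of the DiD. The conclusion rests on a replacement rate close to 80% and on nothing else relevant changing exactly at the cut-off. With a rate between 75% and 85% and an abrupt switch of formula, the jump is at most 3.75 SEK before 2002 and 7.5 SEK after. It should be fixed before analysis, but is not fatal to RQ#1, since the planned DiD is unaffected.

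**What to change.** Choose one of two routes and state the estimand.

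- **Regression kink.** Estimate the change in slope of the outcome at the cut-off and divide by the change in benefit slope (about 0.8). Expect a kink at 75 SEK before 2002 and at 150 SEK after. Let the cut-off follow the flat rate in force in each year.
- **DiD as the main RQ#1 analysis**, preferably with exposure coded as the benefit gain: 60 SEK up to an income of 75, 120 minus 0.80 x income between 75 and 150, and 0 above.

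In either case, say that absence of a level jump at these cut-offs is not evidence of no effect.

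The registers stay the same; the cost is protocol wording and a different local model. The kink route loses precision and needs a wider bandwidth. In the illustration above, with 200 000 parents in the window and a 1% rate, an effect of -0.30 points for a 60 SEK rise gave a mean kink estimate only 0.0000573 / 0.0000344 = 1.7 SDs from zero. The article does not give the number of parents near each cut-off, so feasibility for psychiatric hospitalisation should be checked first; if it is poor, that favours the DiD.

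### The RQ#1 regression discontinuity uses each income line in one period only, although the benefit there changes slope rather than level, so the plots alone cannot separate the 2002 doubling from ordinary curvature

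*Protocol article*

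**What the plan says.** All references are to the Protocol article.

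- *Study design and statistical analyses*, RQ#1, sets the target: "We will examine the effects of the 2002 doubling of flat-rate benefits on the mental health of parents".
- The RD is described as follows: "An RD design will be applied to plot psychiatric hospitalisation rates with labour income as a forcing variable". One line is assigned to each period: "with separate plots before (with an income cut-off equivalent to 75 SEK, at 80% reimbursement rate) and after 2002", then "and after 2002 (with a cut-off equivalent to 150 SEK daily". The remark that both parents' cut-offs will be examined refers to mother and father, not to both lines in both periods.
- *Policy reforms* gives the benefit levels: "the doubling of the general flat-rate benefits from 60 SEK per day (from 1987) to 120 SEK per day (in 2002".
- The same RQ#1 paragraph adds a second analysis: "We will triangulate our findings with a DiD approach, comparing those eligible for the increased benefits to those ineligible before and after reforms".
- The checks named for RD designs are the McCrary density test and a descriptive comparison of the two sides. *Additional analyses* says falsification dates and falsification outcomes, such as prebirth hospitalisations, will be considered. It names no falsification income line.

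**The concern.** RQ#1 asks what the 2002 doubling did. A plot at one income line in one period has no before-after contrast. Comparing the 75 SEK plot with the 150 SEK plot changes the period and the income level together.

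The benefit is also continuous at both lines, so any policy signal there is a change of slope. A smooth, curved relation between income and illness produces an apparent slope change too when straight lines are fitted on each side. Such a relation is plausible at these low incomes: *Unintended health consequences of the Swedish parental leave system* itself expects long-term illness to go with weak labour market attachment.

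If rates fall with income and flatten out, the false slope change is positive. A protective benefit effect makes it negative. Curvature could then mask a benefit or, if strong, look like harm.

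**Working it through.** **1. Reproduce the cut-offs.** The line is the flat rate divided by the reimbursement rate: 60/0.80 = 75 SEK and 120/0.80 = 150 SEK. Both match the protocol.

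**2. Benefit schedule implied by those figures.** With y the daily income, the benefit is max(60, 0.8y) before 2002 and max(120, 0.8y) after.

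| Line | Period | Jump in benefit | Slope left, right | Slope change |
|---|---|---|---|---|
| 75 | before | 0 | 0, 0.8 | 0.8 |
| 75 | after | 0 | 0, 0 | 0 |
| 150 | before | 0 | 0.8, 0.8 | 0 |
| 150 | after | 0 | 0, 0.8 | 0.8 |

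On this schedule each line is active in one period and inactive in the other. The plan uses only the active one.

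**3. How far curvature can mislead, under assumptions.** The protocol gives no rates, bandwidth or polynomial order, so these inputs are assumed: rate per 1,000 = 4 + 8·exp(-y/k) with k = 75, 150 or 300 SEK; triangular-kernel fits on each side; bandwidth h = 25, 50 or 75 SEK; no sampling noise. With no benefit effect, local-linear fits give these false slope changes (per 1,000 per SEK):

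| k | h | at 75 SEK | at 150 SEK |
|---|---|---|---|
| 75 | 25 / 50 / 75 | 0.0105 / 0.0214 / 0.0329 | 0.0039 / 0.0079 / 0.0121 |
| 150 | 25 / 50 / 75 | 0.0043 / 0.0087 / 0.0131 | 0.0026 / 0.0053 / 0.0079 |
| 300 | 25 / 50 / 75 | 0.0014 / 0.0028 / 0.0042 | 0.0011 / 0.0022 / 0.0032 |

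The false step is at most 0.102 per 1,000 at 75 SEK and 0.037 at 150 SEK, on rates of about 5 to 10. Local-quadratic fits reduce the false slope change to at most 0.0019 in absolute value.

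**4. Add a benefit effect.** Assume -0.01 per 1,000 per SEK of benefit. This is -0.6 per 1,000 for 60 SEK more, about 6 to 12% of rates of 5.08 to 10.23. The true slope change is -0.01 × 0.8 = -0.0080. At h = 50, for k = 75 / 150 / 300:

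- 75 SEK before 2002: +0.0134 / +0.0007 / -0.0052.
- 150 SEK after 2002: -0.0001 / -0.0027 / -0.0058.
- Active minus inactive period at the same line: -0.0080 in all six cases.

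**5. If the curve is not stable.** Let the whole curve rise or fall by 10% between periods. The differenced estimate is then -0.0072 to -0.0088 at 150 SEK and -0.0059 to -0.0101 at 75 SEK.

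**6. The planned DiD.** Compare mean rates over incomes of 1 to 150 and 150 to 400 SEK, weighted evenly (assumed), with no benefit effect. A stable curve gives 0.000. A 10% proportional rise or fall gives 0.30 to 0.36 per 1,000 in absolute value.

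**7. Is 75 SEK inactive after 2002?** *Parental leave eligibility and compensation* gives two income levels for 2020, 82 100 and 117 590 SEK a year. The lower one is 82 100/365 × 0.8 = 179.9 SEK a day, close to the 180 SEK guarantee rate. The same section puts the guarantee rate at 60 SEK from 1987 and at 180 SEK only since 2006, and 60/0.8 = 75 SEK. If the lower income level followed the guarantee rate in 2002, a threshold may have remained at 75 SEK. The document does not give the 2002 rule, so this is open.

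**The case against.** The strongest reply is that RQ#1 does not rest on the RD alone. The DiD compares both periods and removes a stable income gradient, as step 6 confirms. This stands. A reader might infer that RQ#1 as a whole cannot tell curvature from a benefit effect, and the protocol does not support that. But the DiD is offered as triangulation, which is worth most when each analysis can be read alone. It also depends on parallel trends, which the protocol undertakes to examine.

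Second, prebirth hospitalisations are named as a possible falsification outcome. Run through the same RD, they could expose a pre-existing bend at the same line and in the same period. This stands in part: the check is only to be considered, and it follows a sentence confined to interrupted time series ("For all ITS designs, we will specify multiple intervention points to assess the possibility of lagged policy effects"), though it is not itself so restricted.

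Third, the protocol never says that a slope change will be read as the effect. A conventional step is hardly biased by curvature. This stands and limits the point. On the protocol's figures, however, the benefit has no step at either line, so a step analysis would look where no benefit contrast exists.

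Fourth, the curve, bandwidth and straight-line fit are assumed, and an article may leave bandwidth and polynomial order to a fuller plan. This also stands. A reader might take the false slope changes above as the expected bias, but the documents fix none of these inputs. The pairing of one line with one period, by contrast, is stated.

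Finally, a reader might take both lines as clean placebos in their unused period. Step 7 shows that this is not established at 75 SEK.

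**Conclusion.** The point holds for the RD part of RQ#1. On the stated benefit levels and reimbursement rate, the contrast at each line is a slope change of 0.8 with no jump. A single-period plot does not by itself isolate the 2002 doubling, and curvature can be mistaken for, or hide, the signal. Neither the density test nor the descriptive comparison of the two sides tests curvature.

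The size is conditional. For the assumed curves with local-linear fits at a 50 SEK bandwidth, the false slope change at 150 SEK is 0.0022 to 0.0079 against an assumed true change of 0.0080 in absolute value, that is 28% to 99% of it. Quadratic fits nearly remove it, and a step estimate is barely touched. This is a low-cost improvement to one of two planned analyses, not a flaw that invalidates RQ#1.

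**What to change.** - State that the RD contrast in RQ#1 is a change of slope (a kink), not a step.
- Fit the 150 SEK line before 2002 with the same model and bandwidth as after 2002, and report that fit as a placebo.
- Take the after-minus-before difference in slope change at 150 SEK as the RD estimate of the reform, using birth years close to 2002 so that nominal incomes are comparable.
- Also show the 75 SEK line after 2002. Treat it as a placebo only once it is confirmed that no eligibility or benefit threshold remained there.

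The cost is two more fits on data already planned for and a few sentences. The difference has a larger variance than a single-period estimate: if the two periods are independent and equally precise, its standard error is √2 ≈ 1.41 times as large. It is exact only if the income-illness curve is stable across the two periods.
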